#### Comparator

The control group receives standardized patient education four times during the 8-week intervention period. Each session lasts 60 minutes, and consists of information regarding: anatomy, physiology, COPD (causes and mechanisms), nutrition, aids/tools and energy saving procedures. The information is the same as for the intervention group, but given on separate occasions. After post-tests, the participants in the control group will be offered participation in a training intervention.

##### Standardization

To enhance repeatability of patient education, the following key elements are being standardized:

Patient education material is standardized and the same for all locations.

Physiotherapists give informed consent to follow the standardized instructions regarding the patient education materials.

### Screening tests and outcome assessment

Different tests will be performed before the start of the study and directly after the 8-week intervention period at Norrlands University Hospital, Umeå, and Karolinska University Hospital, Huddinge. Participants at Örnsköldsvik Hospital, Örnsköldsvik, will perform tests at Norrlands University hospital, Umeå, due to lack of specific test equipment. The primary outcome measures will be assessed by the same researcher (AN) for all participants at each location. Pre-tests will be performed on four occasions, within 3 weeks, before the start of intervention, and post-tests will be performed on three occasions within 2 weeks. Each test occasion will last from 1 to 2 h. Pre- and post-tests will be performed at the same time of day, with the same rest between test occasions and during tests. Since a subject's motivation may determine attainment of maximal effort [7], both pre- and post-tests are performed using standardized information and encouragement [32]. No additional follow-up apart from directly after the end of the intervention period is used within this trial. However, previous studies show that the benefits of exercise training on exercise capacity and QoL in patients with COPD appear to decline by 12 to 24 months despite different exercise strategies [40,41]. There is an urgent need to find effective strategies on how to maintain the positive effects for a longer period. Therefore, in connection with the study described in this protocol, a randomized controlled study is planned to evaluate the effect of motivational interviewing as a strategy to maintain/increase the level of physical activity after a training program (and by that also the benefits achieved from the training program). Participants randomized to the intervention group will be asked to participate, and follow-up tests will be performed at 6, 12 and 24 months. A trial protocol will be published with further description.

### Screening tests

#### Pulmonary function testing

Spirometry, body plethysmography, and single-breath diffusing capacity maneuver will be performed using the Jaeger Masterscreen Body (CareFusion, GmbH, Hoechberg, Germany) at Umeå University Hospital or at Huddinge University Hospital in accordance with recommended techniques [42,43].

#### Cardiopulmonary exercise testing - incremental

Symptom-limited exercise tests will be conducted on an electronically-braked cycle (Rodby RE 990 1063, Hagby, Sweden) at the Department of Clinical Physiology, Umeå University, and at Karolinska University Hospital, Huddinge, in accordance with clinical exercise testing guidelines [44]. An incremental exercise test with work rate increments of 10 Watts per minute until symptom limitation will be performed. Patients will rate their dyspnea and leg fatigue according to the Borg CR-10 scale [20] every minute during the test. Watts maximum (W_max_) is defined as the greatest work rate that the subject is able to maintain for at least 30 s.

### Outcome measures

#### Cardiopulmonary exercise testing – constant work rate

Constant work rate exercise tests will be performed at 75% W_max_ (obtained from cardiopulmonary exercise testing (CPET) – incremental test). Endurance time will be recorded as the time from the increase in work rate to 75% W_max_ to the point of symptom limitation. During the constant-load exercise test, measurement of ventilation, oxygen uptake and carbon dioxide production will be measured by ergospirometry (VMAX Encore 229, CareFusion, Palm Springs, USA in Huddinge and Jaeger Oxycon, CareFusion, GmbH, Hoechberg, Germany in Umeå). CPET is considered the gold standard for measuring the level of exercise limitations of a patient and is often used in patients with COPD [45].

#### Field test

The following tests will be performed at the department of Community Medicine and Rehabilitation, Physiotherapy, Umeå University, and at the Physiotherapy division in Karolinska University Hospital, Huddinge: dyspnea and muscle fatigue in the legs and arms, depending on the test, will be measured with the Borg CR10 [46], and oxygen saturation and pulse will be measured with pulsoximetry (Nellcore NPB-40, Pleasanton, CA, USA) before and directly after each test. The Borg CR10 scale has previously been used to evaluate dyspnea, breathlessness and leg discomfort in COPD patients [47] and is found to be reliable [48].

##### Upper extremity

*Primary outcome:* To assess functional muscular capacity in the upper extremity, the 6-minute pegboard and ring test will be used [49]. The pegboard and ring test consists of a peg board with the pegs set at the subject’s shoulder height and 10 cm below shoulder height. The pegs will be at shoulder width; three different insertions are available (45, 50 and 55 cm width) to be suitable for all participants. The rings consist of 10 lightweight wooden rings (6 g each) that the subject moves simultaneously from the upper pegs to the lower pegs repeatedly [50]. The subjects are asked to move as many rings as possible in 6 minutes and the final score is the total number of rings moved in the given amount of time. Standardized encouragement will be given to the subjects each minute. All subjects will move 20 rings from the lower to the upper pegs and reverse prior to the test to familiarize themselves with the test procedure and lower the risk for learning effect. The 6 minute pegboard and ring test has previously been used on COPD patients [51] and shows excellent test-retest reliability [49]. To measure unsupported endurance capacity, the Unsupported Upper Limb Exercise test (UULEX) will be used [52]. The patients hold a plastic bar (0.2 kg) at shoulder width. The UULEX consists of eight levels; the patients perform each level for 1 minute, lifting the plastic bar at a cadence of 30 beats per minute, controlled with a metronome, from the hip to the UULEX eight level chart. The tests starts with a 2-minute warm up at the lowest level; the warm up is included in the final time. The first level is adjusted to be at the level of the patient’s knees by altering the position of the UULEX chart on the wall. Once they have reached their maximum height the bar will be replaced with a heavier one (0.2 < 0.5 < 1 < 1.5 < 2 kg). The patients are instructed to perform the test until symptom limitation. The UULEX has previously been used on COPD patients [51].

##### Lower extremity

*Primary outcome:* The 6 MWT will be used to assess lower extremity functional muscular endurance and walking capacity. The 6 MWT is widely used on COPD patients for measurement of endurance walking capacity [53]. In this study we expect to see a difference of 50 m based on a recent published RCT on unsupported training and COPD [54]. The walking course will be 30 m in length and the patients will be instructed in accordance with standardized guidelines [55] to walk as far as possible in 6 minutes. One practice test will be performed to minimize risk of learning effect. The highest value will be chosen as the baseline value.

#### Peripheral muscle strength

Isokinetic muscle strength (maximal and endurance) in the leg (knee extension) and the arm (shoulder flexion) will be evaluated by the use of two interchangeable stationary dynamometers: the Biodex Multi-Joint System 3 (Biodex Corp., Shirley, NY, USA) at the Department of Community Medicine and Rehabilitation, Physiotherapy, Umeå University; and The Biodex Multi-Joint System 4 (Biodex Corp., Shirley) at Karolinska University Hospital, Huddinge. The tests will be performed unilaterally on the self-reported, dominant side. Subjects will be seated in accordance with the manufacturer’s recommendations. The 6 MWT is performed before the isokinetic tests and will be considered as a warm-up. Before both maximal tests the participants will perform five submaximal contractions to familiarize themselves with the equipment and testing procedure, followed by 2 minutes standardized rest before the start of testing [32].

##### Shoulder flexion

Test of shoulder flexion will be performed between 0° and 100°; great care will be taken to align the glenohumeral joint with the movement axis of the Biodex dynamometers (The Biodex Multi-Joint System 3 and 4 (Biodex Corp., Shirley)). The arm will be held with the elbow extended and the forearm semi-pronated [56].

##### Knee extension

The test of knee extension will be performed between 90° flexion to maximal knee extension −5°. Full extension −5° will be used to lower the risk for a passive resistance from the hamstring muscle during knee extension. Great care will be taken to align the lateral femur epicondyle with the movement axis of the Biodex dynamometers (The Biodex Multi-Joint System 3 and 4 (Biodex Corp., Shirley)). Positioning of participants, equipment, and range of motion will be documented to be the same during pre- and post-tests. Two different aspects of isokinetic muscle strength will be measured. Firstly, a maximum contraction test measuring peak torque (Nm) from the highest contraction at an angular velocity of 60°·per s, generated through five maximal contractions, will be performed as previously used and recommended for COPD patients [57-59]. The subjects are told to flex their arm or extend their leg five times in a row with maximal effort during the concentric phase and to rest during the eccentric phase. Secondly, after a recovery period of 5 minutes [32,59], an endurance test consisting of 30 consecutive repetitions [59] at 60°·per s measuring total work (joules) will be performed. The subjects are told to flex their arm or extend their leg 30 times using maximal effort at each repetition during the concentric phase and to rest during the eccentric phase. The angular velocity of 60°·per s is considered ideal for evaluating muscle strength in COPD patients [57] and is found reliable in endurance tests [60]. No visual feedback is given during tests. Standardized encouragement is given.

#### Chronic dyspnea questionnaires

The Medical Research Council (MRC) Dyspnea scale is a five-point scale based on degrees of various physical activities that cause dyspnea [61] and will be used to grade the patients’ inconvenience. The MRC dyspnea scale has been used in numerous clinical trials involving COPD [62], and is shown to be valid in COPD patients [63].

#### Health-related quality of life

##### Primary outcome

The CRQ-SAS version of the CRQ [64] will be used to assess QoL. The CRQ is a widely used disease specific questionnaire to assess symptoms of COPD patients [65]. The Swedish CRQ-SAS consists of 20 health-related questions. The Swedish version of the Clinical COPD questionnaire (CCQ) will also be used to assess disease-specific QoL [66]. The CCQ has been shown to be valid and reliable in Swedish patients with COPD [67] and consists of 10 questions. The Swedish SF-36 will be used for the assessment of QoL. SF-36 is a 36-item questionnaire used to evaluate QoL through eight subscales: physical functioning, role-physical, role-emotional, social functioning, general health, mental health, bodily pain and vitality [68]. The SF-36 has previously been used in the assessment of QoL in COPD patients [69] and is considered the gold standard generic health assessment tool [70], being both valid, reliable and vigorously tested [68].

#### Anxiety, depression and self-efficacy

The Hospital Anxiety and Depression Scale (HADs) will be used for assessment of anxiety and depression. HADs consists of 14 items, producing separate scores for anxiety and depression [71]. The questionnaire is widely used in association with COPD [72]. The Swedish version of the Exercise Self-Efficacy Scale (ESES) [73] will be used to investigate self-efficacy. The ESES consists of 10 questions and the Swedish version is now undergoing validity and reliability tests.

The Self Efficacy for Walking Questionnaire will be used to assess the patients self efficacy in association with physical activity, and the questionnaire has been used in intervention studies on patients with COPD [74].

#### Feasibility

Feasibility will be evaluated through attendance, adherence and development of any side effects or injury during each training session. In addition, compliance to the different parts of the HRSLE will be evaluated with a standardized questionnaire by both study participants and the physiotherapists leading the interventions.

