**Consolidate standards of reporting trials** (**CONSORT) flow diagram of trial design.**

### Objectives

The aim of the current randomized controlled multicenter trial (RCT) is to determine the effects of high-repetitive single limb exercises (HRSLE) in combination with COPD-specific patient education, compared to the COPD-specific patient education alone in patients with moderate to very severe (stage II-IV) COPD.

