#### Secondary outcomes

1. Determine the effect of HRSLE on: 1) endurance time, ventilatory response, perceived dyspnea and leg fatigue during submaximal cycle test; 2) maximal strength and muscular endurance during isokinetic tests; and 3) self reported dyspnea, self-efficacy, anxiety and depression.

2. Determine the relationship between: 1) changes in self reported dyspnea, self-efficacy, anxiety and depression; and 2) changes in exercise capacity

3. Identify if there are any sex-related differences in exercise training effects.

4. Determine if this exercise regimen is feasible and safe in stage II-IV COPD patients.

5. Develop a strategy to minimize attempts needed to determine a multiple repetition resistance using elastic bands.

6. Develop a strategy to optimize resistance for each involved movement within an exercise regimen.

7. Investigate the relationship between muscle fatigue and dyspnea in the different exercise tests.

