#### Physiotherapist education

All physiotherapists leading the HRSLE will receive individual standardized education before the start of intervention. The education lasts for 60 minutes and consists of written, oral and visual instructions on how to perform and instruct each exercise within the HRSLE. It also includes instructions on how to progress exercise with the use of Borg CR10 [20], and how to standardize exercises and positions during warm-up, training and cool-down within the HRSLE regimen.

The written information includes:

(1) A check-list for all sessions on what to do, before, during and after each session (including placement of equipment, exercise order, when to rate muscular fatigue and dyspnea with Borg CR10, and use of pulsoximetry).

(2) A comprehensive exercise protocol (see Additional file 1).

(3) Rating sheets for muscular fatigue, dyspnea and saturation.

(4) The written information given to participants in:

a. The intervention group

b. The control group

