### Description of intervention and comparator

#### Intervention treatment

The HRSLE regimen consists of three sessions per week (Monday, Wednesday and Friday at approximately noon) during 8 weeks of exercise training, giving a total number of 24 sessions. The HRSLE regimen is supervised and conducted by local physiotherapists using a group format, with four to eight participants in each group. Each session will span approximately 60 minutes duration for the major components: 10 minutes warm-up followed by 40 minutes of HRSLE, and then 10 minutes cool-down.

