The targeted velocity - that is, 1 s concentric, 1 s eccentric (60 beats/minute) - for seven out of eight exercises is standardized by counting by the physiotherapist leading the training sessions. In addition, music at twice the pace (around 120 beats/minute) will be used to assist the physiotherapists and patients.

The standardized exercise protocol (Additional file 1) will be given to both participants and physiotherapists to enhance adherence and familiarization.

Patient education material is standardized and the same for all locations.

Physiotherapists are given standardized education to uniformly deliver the intervention.

In addition to the exercise protocol, standardized instructions on exercise progression and distance from elastic resistance insertion for each exercise (as described above) will be given to the physiotherapists leading the training to enhance adherence. Furthermore, written commitments to follow the assigned protocol will be signed by all physiotherapists and adherence to trial protocol will be evaluated by a questionnaire after the end of intervention for both participants and physiotherapists.

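### Harms are recorded in connection with training sessions, so the safety aim can be answered only descriptively in attending exercise patients, with no control count

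*Protocol article*

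**What the plan says.** The fourth item under Secondary outcomes is: "Determine if this exercise regimen is feasible and safe in stage II-IV COPD patients". The Feasibility section gives the only description of how harms are noted: "Feasibility will be evaluated through attendance, adherence and development of any side effects or injury during each training session".

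The exercise arm trains three times a week, "during 8 weeks of exercise training, giving a total number of 24 sessions" (Intervention treatment). For the other arm, "The control group receives standardized patient education four times during the 8-week intervention period", and "After post-tests, the participants in the control group will be offered participation in a training intervention" (both under Comparator).

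Two other recording tools are described. The physiotherapists' written material includes "Rating sheets for muscular fatigue, dyspnea and saturation" (Physiotherapist education). Under Standardization of the intervention, "adherence to trial protocol will be evaluated by a questionnaire after the end of intervention for both participants and physiotherapists". Neither tool is described as collecting adverse events.

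The Statistics section applies intention-to-treat to every outcome, brings all randomized patients into the analysis of secondary as well as primary outcomes, and promises a summary of each outcome in each group.

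**The concern.** The trial's overall aim is comparative: exercise plus education "compared to the COPD-specific patient education alone in patients with moderate to very severe (stage II-IV) COPD" (Objectives). Patients with COPD of this severity can have exacerbations and other events without any training. The plan treats exacerbations as important enough to appear in both the inclusion and the exclusion criteria, yet the article does not describe counting them after randomization. Without a count from controls over the same 8 weeks, events in the exercise arm have no background rate beside them.

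A rule tied to sessions also depends on attendance. A patient who stops because of an injury or an exacerbation has no further sessions at which it would be noted, so the record is thinnest where harm is most likely to have occurred. A published safety statement would then rest on a partial count from one arm, weighted towards those who tolerated the training.

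**Working it through.** **The plan's own figure.** The article gives no figure for safety. The only number used here is the arm size, which reproduces from the Sample size section: 17 / (1 − 0.20) = 21.25, rounded up to 22 per arm, 44 in total.

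**Harms observation by arm in the randomized period, under the stated rule**

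| | Exercise | Control |
|---|---|---|
| Training sessions per patient | 3 × 8 = 24 | 0 |
| Patient-sessions at which harms are noted, at most | 24 × 22 = 528 | 0 × 22 = 0 |
| Education sessions per patient, where the article describes no harms question | 4 | 4 |
| Post-test occasions, where the article describes no harms question | 3 | 3 |

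The contacts needed for equal collection already exist in both arms. What differs is where harms are said to be noted.

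**Patients who stop.** At the expected 20% drop-out, 0.20 × 22 = 4.4, so about 4 patients per arm. How many of these would leave because of an event is not known from the document.

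**Fit with the analysis rule.** Safety stands in the list of secondary outcomes. The Statistics section wants all randomized patients in each analysis and a summary for each group. Under the Feasibility rule, the 22 controls, half of those randomized, contribute no harms data, so neither condition can be met for this item.

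**Precision.** With zero events among n patients, the exact one-sided 95% upper limit for the event risk is 1 − 0.05^(1/n):

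- n = 22: 1 − 0.05^(1/22) = 12.7%
- n = 17: 1 − 0.05^(1/17) = 16.2%

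The upper end of the two-sided exact 95% interval is 1 − 0.025^(1/22) = 15.4% for n = 22. These limits depend on n alone. They would be the same with continuous recording.

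**What a two-arm count could show.** The risks below are assumptions for illustration; the document gives none. Two-sided α = 0.05, 22 per arm.

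| Assumed risks | Power, normal approximation | Power, Fisher's exact test |
|---|---|---|
| 10% vs 30% | 38% | 28% |
| 10% vs 50% | 85% | 79% |

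Equal collection would support a formal comparison only for very large differences. Its value lies in a like-for-like description.

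**The case against.** The strongest reply is that this is a condensed article. The Feasibility section describes how feasibility is judged. It does not claim to be the whole adverse-event procedure, and nothing in the article says that events between sessions or in controls go unrecorded. A reader might infer that controls will have no harms record at all; the document does not establish that, because a fuller protocol may contain general event reporting. This limits the point to what the article describes. It does not remove it, because the article does state a rule, and that rule does not suit the aim beside it.

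A reader might also infer that the safety question cannot be answered. That goes too far. The aim concerns the regimen, is paired with feasibility, and promises no between-arm safety comparison. Up to 528 supervised patient-sessions, with saturation and dyspnea ratings, give a real if limited descriptive answer. Several other secondary items, such as finding the right resistance, are one-arm by nature.

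A third tempting reading is that only 24 of 8 × 168 = 1,344 hours, or 1.8%, are observed. That takes the wording on timing at its narrowest. It may equally mean that patients are asked at each session; with sessions on Mondays, Wednesdays and Fridays, a delayed complaint in an attending patient could then surface within two or three days. The 1.8% is therefore not a measure of missed harm. On either reading, controls and patients who no longer attend stay outside the rule.

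Finally, attendance is recorded, so stopping is visible, and both arms complete dyspnea and quality-of-life questionnaires before and after. This is true, but these instruments do not count events or give the reason for stopping.

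**Conclusion.** The point holds in limited form. As described, the method gives no harms data for controls during the randomized period and may miss events in exercise patients who stop attending. The secondary safety aim can be answered only as a description of attending exercise patients, without a background count, and this does not match the Statistics section's own rule for secondary outcomes. The conclusion assumes that the Feasibility section is the operative rule; a fuller protocol with collection in both arms would reduce it to a clarification.

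The primary outcomes are unaffected. The 12.7% limit shows how little 22 patients can establish about safety, but it follows from sample size and is not evidence against the recording rule. The change is worth making because it is cheap, and because events not asked about during the trial are hard to recover reliably afterwards.

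**What to change.** 1. Ask the same short set of questions in both arms (exacerbations, injuries, other adverse events, and withdrawal because of any of these) at each of the four education sessions and at the post-tests, with a brief telephone call to those who stop.
2. Base the between-arm count on these common contacts only. Report the training-session record separately as a one-arm table; otherwise the exercise arm, with 24 extra contacts, would be asked more often.
3. At the post-tests, use a self-completed form or someone other than the blinded outcome assessor, since an answer about a training injury would reveal the allocation.
4. Report the number of patients with events by randomized arm with exact 95% confidence intervals and no formal test.
5. Reword the secondary aim as describing harms.
6. If the full protocol already provides for such collection, say so in the Feasibility section. Recruitment was under way at submission, so if the collection is new, state from which date it applies.

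The cost is one short form at visits both arms already attend, a few telephone calls (about 4 patients per arm at the expected drop-out) and a little data entry. The comparison remains imprecise at 22 per arm, and the report should say so.
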